### Statistical analyses

Analysis of the patients will follow the CONSORT flow diagram (Fig. 1) through the phases of the study (enrollment [assessed, excluded, randomized], allocation [control group and experimental group with intervention received or not received], follow-up [lost to follow-up, discontinued intervention] and analysis) [30].

All statistical analyses will be conducted using SPSS software version 22 (IBM, Armonk, NY, USA). All tests will be two-sided and significance will be set at *P* < 0.05. Efficacy measurements were adjusted by intention-to-treat analysis. Missing values will be replaced using the last observation carried forward (LOCF) method. No subgroup analyses are planned. Standard deviations, 95% confidence intervals, and median will be used for the descriptive analyses. Primary and secondary outcome analysis: the Chi-square test or Fisher’s exact test will be employed to identify any objective outcome differences among groups.

Generally, continuous data will be checked for normality using the Shapiro–Wilk test. If the normality assumption is violated, then PISQ-12 and PFDI scores as tertiary outcomes will be normalized by log transformation (log10(x)). Univariate-repeated measure analysis of variance (ANOVA) will be used to determine the secondary outcome between and within the two groups (mTVM, TVM group) at six endpoints (before intervention and during follow-up clinical appointments 1–5 following intervention). Mixed design ANOVA will be carried out to determine the effects of the modified operation on subjective cure rate for POP and SUI, and the Bonferroni post hoc test will be used to test the difference between means. All statistical analyses will be completed after the final measurement of the last patient during the last clinical appointment after intervention. The repeated measure design with seven points in time allows us to monitor how patients change over time in both short-term (before/during intervention) and long-term situations (before/after intervention).

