#### Participants considered for trial

This will be a prospective longitudinal study involving all patients successively scheduled for operation for symptomatic prolapse POP–Q grade II or III and coexisting SUI, who will be included in the study after informed consent has been obtained. Patients will be recruited in the Department of Obstetrics and Gynaecology at the University of Szeged. The study will be conducted for an estimated maximum of 18 months (between August 2016 and December 2017). Table 1 provides an overview of the patient recruitment and evaluation plan.

**Table 1 Tab1:** Schedule of assessments/data collection

Assessment	Recruitment before intervention phase	Intervention (surgery)	Follow-up				
			6 weeks	6 months	1 years	2 years	3 years
Assessment of eligibility criteria	x						
Written informed consent	x						
Gynecological examination: incontinence symptoms	x	x	x	x	x	x	x
Gynecological examination: prolapse	x	x	x	x	x	x	x
Urodynamic examination	x				x		x
Adverse events		x	x	x	x	x	x
Questionnaires: PISQ-12 and PFDI	x		x	x	x	x	x
Introital sonography	x				x		x
Urine culture	x			x	x	x	x

The symptomatic POP–Q Stage II–III (determined by the gynecological examination using the International Continence Society quantification system) [18] anterior vaginal wall prolapse is defined as the maximum extent of the prolapsed anterior and middle compartments being within 1 cm above and 6 cm below the hymen [19, 20]. According to the international POP guidelines (the EBU and NICE guidelines) [21, 22], if the condition disrupts the patient’s life and non-surgical treatment options have not helped, it should be treated surgically.

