### Primary endpoints

The primary outcome measures will be a significant improvement in POP repair and objective cure of SUI after the surgery. The efficacy of POP repair will be understood as a significant (> 3 cm) improvement during follow-up at points Aa, Ba, C, and D using the POP–Q system (International Continence Society) [19, 20]. Anti-incontinence efficacy is classified as no further SUI, as diagnosed by cough tests and urodynamic examinations. Besides the gynecological and urodynamic examinations, sonographic findings from introital ultrasound examinations will be analyzed in terms of anatomical success both before and following surgery and during follow-up.

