#### Sample size calculation

As we have newly developed the modification to the prosthesis surgery, an exploratory pilot study was designed to evaluate the feasibility of the modification to the mesh for the treatment of SUI. Twenty patients with SUI and POP were recruited for a mTVM operation by the same two senior surgeons who are conducting this randomization study. The sample size calculation study was designed based on preliminary data on the 20 patients. The newly developed technique yielded an objective SUI cure rate of 92% as opposed to 72% for the original TVM published by Sergent et al. [13, 17]. Sample size calculations were performed with G*Power software [29], using the statistical model for an χ^2^ approach. Consequently, sample size was estimated theoretically and an effect size of = 0.1, indicating a small effect, will be accepted. The sample size was calculated for the primary outcome of the SUI cure rate with the following assumptions: α = 0.05, power (1–β error probability) = 0.8, number of groups = 2. Based on these assumptions, a total sample size of *N* = 130 was estimated. In anticipation of dropouts (10%: *n* = 16) or a violation of protocol (10%: *n* = 16), a final sample size of *N* = 162 (81 participants per group) results.

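### LOCF for all missing values can carry early dryness, or a preoperative positive urodynamic test, into the SUI cure endpoint, and can bias it in either direction

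*Protocol article*

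**What the plan says.** Under Statistical analyses, the protocol article states "Missing values will be replaced using the last observation carried forward (LOCF) method". The sentence before it reads "Efficacy measurements were adjusted by intention-to-treat analysis", so the completed data are analysed as randomised. For the primary and secondary outcomes, "the Chi-square test or Fisher’s exact test will be employed to identify any objective outcome differences among groups". PISQ-12 and PFDI go into repeated-measures and mixed-design ANOVA.

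Primary endpoints defines SUI cure as follows: "Anti-incontinence efficacy is classified as no further SUI, as diagnosed by cough tests and urodynamic examinations". It names no single primary visit.

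Table 1 schedules the two parts of that definition differently:
- The row "Gynecological examination: incontinence symptoms" is marked at every visit: before surgery, at surgery, 6 weeks, 6 months, and 1, 2 and 3 years.
- The row "Urodynamic examination" is marked only before surgery and at 1 and 3 years.

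Every participant enters with "symptomatic prolapse POP–Q grade II or III and coexisting SUI", so cure at baseline is 0% in both arms.

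Sample size calculation assumes 92% vs 72% cure. It allows 10% for dropout and 10% for protocol violation, and reaches 162 women, 81 per group.

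**The concern.** LOCF assumes that a woman's status stays fixed after her last observation. The protocol does not treat status as fixed: it lists recurrent incontinence among the reasons for reoperation and follows patients for 3 years.

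Two errors can follow, in opposite directions.

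- **Dryness carried.** A woman who is dry at 6 weeks or 6 months and is then lost counts as cured at 1, 2 and 3 years.
- **Wetness carried.** No postoperative urodynamic test is scheduled before 1 year. A woman who misses that test has only her preoperative SUI-positive result to carry, and it would sit beside a postoperative cough test. Scored by component, she becomes a surgical failure on a measurement made before surgery.

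At stake are the cure rate in each arm, the difference between arms and, where loss is unequal, the type I error of the primary test. For PISQ-12 and PFDI, the ANOVA would also treat filled-in scores as observed ones.

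**Working it through.** **The plan's own figures.** Inputs from Sample size calculation and Statistical analyses: 92% vs 72%, two-sided α = 0.05, power 0.80, 1:1. Fisher's exact test reaches 0.806 at 64 per arm (total 128) and 0.814 at 65 per arm, so 130 is reproduced closely. Inflation: 130/(1 − 0.20) = 162.5, which matches 162. I use 81 per group because under intention-to-treat with LOCF every randomised woman is analysed.

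**Assumptions not in the document:** loss by arm, early cure rates, and one late visit as the analysis visit.

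**Formulas.** With d the fraction missing in an arm:

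cure under LOCF = (1 − d) × true late cure + d × carried cure

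Power ≈ Φ[(D − 1.96·s0)/s1] + Φ[(−D − 1.96·s0)/s1], where D is the difference, p̄ the mean of the two rates, s0 = √(2p̄(1−p̄)/n) and s1 = √((p1(1−p1)+p2(1−p2))/n).

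**Results at n = 81 per arm, true late cure 92% vs 72%:**

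| Carried value (mTVM / TVM) | Missing (mTVM / TVM) | Cure under LOCF | Difference | Power |
|---|---|---|---|---|
| none missing | 0 / 0 | 92.0 vs 72.0 | 20.0 | 0.92 |
| dry 97% / 85% | 10% / 10% | 92.5 vs 73.3 | 19.2 | 0.91 |
| dry 97% / 85% | 20% / 20% | 93.0 vs 74.6 | 18.4 | 0.90 |
| dry 97% / 97% | 10% / 10% | 92.5 vs 74.5 | 18.0 | 0.88 |
| dry 97% / 97% | 20% / 20% | 93.0 vs 77.0 | 16.0 | 0.82 |
| wet (0 / 0) | 10% / 10% | 82.8 vs 64.8 | 18.0 | 0.75 |
| wet (0 / 0) | 20% / 20% | 73.6 vs 57.6 | 16.0 | 0.57 |
| wet (0 / 0) | 5% / 15% | 87.4 vs 61.2 | 26.2 | 0.97 |
| wet (0 / 0) | 15% / 5% | 78.2 vs 68.4 | 9.8 | 0.29 |

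Example, wet at 10% / 10%: 0.9 × 0.92 = 0.828 and 0.9 × 0.72 = 0.648. p̄ = 0.738, s0 = 0.0691, s1 = 0.0676. (0.18 − 1.96 × 0.0691)/0.0676 = 0.66, and Φ = 0.745. Exact enumeration of the Pearson chi-square gives 0.93 with none missing and 0.75 here.

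Most of that drop comes from LOCF, not from having fewer women. Observed cases only, about 0.9 × 81 = 73 per arm at 92% vs 72%, give s0 = 0.0636, s1 = 0.0614 and (0.20 − 1.96 × 0.0636)/0.0614 = 1.23, so power is about 0.89 by the same formula.

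**No true effect, 80% in both arms, wetness carried:**
- 10% missing in each arm: 72% vs 72%, difference 0, rejection 5%.
- 5% vs 15% missing: 0.95 × 0.80 = 76% vs 0.85 × 0.80 = 68%. s0 = 0.0706, s1 = 0.0703. (0.08 − 1.96 × 0.0706)/0.0703 = −0.83, and Φ = 0.203. The other tail adds 0.001. Rejection is about 20%.
- With early dryness of 95% carried in both arms instead, 5% vs 15% missing gives a rejection rate of only 5.7%.

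**Standard error of the difference at 20% loss:**
- Observed cases (64.8 per arm): √((0.92×0.08 + 0.72×0.28)/64.8) = 0.065.
- LOCF with dryness carried (93.0 vs 74.6, n = 81): 0.056, about 14% smaller.
- LOCF with wetness carried (73.6 vs 57.6, n = 81): 0.074, larger.

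**The case against.** The strongest reply is that the rule is one line in a condensed article. It does not say that LOCF works on the cough test and urodynamics separately, or that a baseline value may stand for a postoperative outcome. Carrying the last postoperative cure classification is an equally open reading, and the wetness mechanism then disappears. This stands in part. A reader might infer that the two components must contradict each other, but that needs component-level LOCF, which the text permits without requiring. The dryness mechanism remains under either reading.

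Second, equal loss only shrinks a true difference, from 20 to about 16–19 points, and leaves no bias when there is no effect and early profiles are equal. The large distortions need unequal loss as well as wetness carried. This also stands. The article gives no loss by arm. It does say that women learn their allocation after the 12-month forms, or earlier after major complications, so unequal later loss is possible but not shown.

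Other stronger readings are not supported:

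- **LOCF always understates uncertainty.** It does so when dryness is carried and for the questionnaire ANOVA. When wetness is carried the nominal standard error is larger and the harm is bias.
- **The trial hypothesises different recurrence by arm.** The stated hypothesis is greater improvement of continence, and the Background speaks of residual SUI. A woman already wet at her first postoperative visit is carried forward as wet, so for her LOCF creates no false cure.
- **Multiple imputation repairs any selective loss.** Assume 6-week dryness of 95% (mTVM) and 85% (TVM), late cure of 92% and 72%, and that half of those who became wet go missing while no dry woman does. LOCF gives 92 + 1.5 = 93.5% vs 72 + 6.5 = 78.5%, a difference of 15.0 points. Imputing by arm from 6-week dryness gives 92 + 1.5 × (92/93.5) = 93.5% vs 72 + 6.5 × (72/78.5) = 78.0%, a difference of 15.5 points. That loss is not at random, so such an example does not measure what changing the primary method would gain. Exact power at 81 per group with LOCF is still 0.81 there.

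**Conclusion.** The point holds in a limited form. LOCF is a stated choice, applied without exception and without a stated sensitivity analysis, in a trial whose cure endpoint combines a test done at every visit with one done only before surgery and at 1 and 3 years. It can turn early dryness into lasting cure. Read component by component, it can also turn a preoperative test into a surgical failure.

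The direction of bias cannot be stated in advance. The 20% rejection rate requires wetness carried and 5% vs 15% loss. The fall in power from 0.93 to 0.75 requires wetness carried and 10% loss per arm. With dryness carried and equal loss, the effect is a few points of attenuation at most. All of these sizes rest on assumed loss and early cure rates. The documents do not show that the main result will be wrong, only that the stated rule leaves it open to avoidable bias.

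**What to change.** Delete the LOCF sentence and state that no preoperative value may stand for postoperative cure.

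- **Binary SUI cure:** multiple imputation by arm, with baseline severity and all available postoperative cough tests and POP-Q values as predictors. At 92% cure the mTVM arm would have only about 0.08 × 81 = 6.5 failures, so the imputation model should be kept simple.
- **Sensitivity analysis:** missing = not cured, because multiple imputation assumes missing at random. For a missing woman this gives the same value as carried wetness, so it is equally exposed to unequal loss. It belongs beside the primary analysis, with missing counts by arm and visit, and should not replace it.
- **PISQ-12 and PFDI:** a likelihood-based mixed model for repeated measures on the observed scores, in place of ANOVA on filled-in data.

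The cost is a change of wording, a little more analysis work and slightly wider intervals. No new patients, visits or measurements are needed. The article places all analysis after the last patient's final visit, so the change can be fixed before any analysis is run.

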In all cases, SUI will be visualized after a complete physical examination is performed (verified by pad test/Bonney test/two-dimensional [2D] introital sonography and urodynamic examination). The severity of SUI was assessed using the Ingelman–Sundberg classification [23]. Urodynamic examinations comprising uroflowmetry, cystometrography, the pressure-flow study, and the abdominal leak point pressure test will be performed before surgery to objectively determine the coexisting symptomatic SUI based on the international guidelines (the EBU and NICE guidelines) [21, 22]. The abdominal leak point pressure test will be used as a standardized examination method for the evaluation of SUI with urine leakage as a sign. If the intra-abdominal pressure recorded at the point of urine leakage was < 40 cmH_2_O, the origin of the SUI was set as intrinsic sphincter deficiency (ISD) [24]. In the case of ISD, preoperative pelvic floor training (PFMT) will be recommended. If the patient is unwilling to participate in PFMT or if the training was unsuccessful, we will recommend mesh surgery. This will also be the case for suspected urethral hypermobility, i.e. if the intra-abdominal pressure at the point of urine leakage was > 60 cmH2O.

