#### Concealment of group allocation from participants

After the screening phase, patients will be randomly assigned to one of the two therapy groups (the TVM group or modified TVM (mTVM) group). The allocation sequence will be generated by the independent urogynecology secretariat using online randomization software (http://randomization.com); allocation ratio = 1:1 (TVM group:mTVM group). The allocation will be concealed in sealed, opaque, sequentially numbered envelopes, which will be stored at the operating theatre. All the women recruited will be numbered consecutively corresponding to the numbered envelopes. The envelope will not be opened until the general narcosis of the study participant has been established. To increase the validity of the trial, the assigned procedure will be blinded for the study participants throughout the follow-up period. The participants will be informed of allocated treatment after completing the study forms 12 months after the procedures. If major complications occur, the study participants and the outcome assessor will be also informed of the allocated treatment at the time of any suspected complication(s).

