### Randomization

The patients will be randomized to one of the study groups using a computer-generated list. Allocation concealment will be ensured by enclosing assignments in sealed, opaque, sequentially numbered envelopes, which will only be opened when the general narcosis of the study patient has been established [26].

Postoperative outcomes and sequalae will be assessed by an outcome assessor who is a gynecologist in a subspecialization program in urogynecology and also well trained in the transvaginal mesh operation. The outcome assessor will remain blinded to the type of intervention throughout the study.

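### The primary SUI cure test is fixed as unadjusted, although a pre-surgery severity grade could be used for a modest gain in efficiency and in protection against chance imbalance

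*Protocol article*

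**What the plan says.** All references are to the protocol article.

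- **Endpoint** (Primary endpoints): SUI cure is binary. "Anti-incontinence efficacy is classified as no further SUI, as diagnosed by cough tests and urodynamic examinations".
- **Test** (Statistical analyses): "the Chi-square test or Fisher’s exact test will be employed to identify any objective outcome differences among groups". Tests are two-sided at 0.05. No covariate or stratifying factor is named. The remark in the same section that efficacy is adjusted by intention-to-treat concerns who is analysed, not baseline covariates.
- **Baseline severity** (Participants considered for trial): "The severity of SUI was assessed using the Ingelman–Sundberg classification". The same section puts leak point pressure before surgery: "The abdominal leak point pressure test will be used as a standardized examination method for the evaluation of SUI".
- **Randomization** (Concealment of group allocation from participants; Randomization): "allocation ratio = 1:1 (TVM group:mTVM group"), and "The patients will be randomized to one of the study groups using a computer-generated list". Neither section states stratification.
- **Planning rates** (Sample size calculation): "objective SUI cure rate of 92% as opposed to 72% for the original TVM". Alpha is 0.05, power 0.80 and N = 130, raised to 162 (81 per group) for losses. The Abstract gives 65 per group.

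**The concern.** The severity grade is the baseline counterpart of the primary endpoint, so it is a natural candidate predictor of remaining incontinence. If it does predict cure, an unadjusted comparison of two proportions leaves its variation in the error term and loses some precision. With no stated stratification, the arms may also differ in severity by chance, and the named test cannot correct the estimated difference for that.

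What is at stake is a few points of power and a possible shift of a few percentage points in the estimated cure difference. A statement made now also prevents a later argument: adjusting only after an imbalance has been seen would not be credible.

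**Working it through.** **1. Inputs.** From the protocol: cure 72% (TVM) and 92% (mTVM), two-sided alpha 0.05, 1:1 allocation, 65 per arm. Assumed: three severity grades with shares 30/40/30%, and an odds ratio (OR) for failure of 1 to 4 per grade. The protocol gives neither the distribution of grades nor their prognostic strength.

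**2. The planned size.** For 80% power at 72% versus 92%, chi-square needs 114–116 in total and Fisher's exact test 64 per arm = 128. The stated 130 is therefore close to the Fisher figure. (The effect size of 0.1 quoted with it would need 785; that is a separate matter.)

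**3. Power of the unadjusted test at 65 per arm.** With mean cure p = 0.82:

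power = Φ{[0.20·√65 − 1.96·√(2·0.82·0.18)] / √(0.72·0.28 + 0.92·0.08)}
= Φ{[1.612 − 1.065] / 0.525} = Φ(1.04) = 85.2%.

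Exact enumeration gives 86.5% for chi-square and 81.4% for Fisher. At 81 per arm, exact chi-square power is 93.0%.

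**4. Power with stratification.** The Cochran-Mantel-Haenszel (CMH) statistic without continuity correction is [Σ(a − E)]² / ΣV on 1 df. In each grade, a is the number of cures under mTVM, and E and V are its hypergeometric mean and variance. Simulation used 20,000 trials per scenario, 65 per arm, with marginal rates held at 72% and 92%:

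| OR per grade (assumed) | Chi-square | CMH, uncorrected |
|---|---|---|
| 1 | about 86% | 86.2% |
| 1.5 | about 86% | 86.5% |
| 2 | about 86% | 87.5% |
| 3 | about 86% | 88.8% |
| 4 | about 86% | 89.9% |

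A run of 40,000 trials agreed within 0.3 points (CMH 86.1, 86.7, 87.5, 89.0 and 90.2% against 86.5%). Type I error was 4.7–5.3% for CMH and 4.6–5.2% for chi-square.

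**5. Cross-check by explained variance.** Dividing 65 by (1 − R²) gives an effective size per arm. R² = 0.05 gives 68.4 and power 86.9%; 0.10 gives 72.2 and 88.7%; 0.20 gives 81.2 and 92.0%. The order of magnitude is the same.

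**6. Chance imbalance.** A factor present in 50% of women differs between arms with SD √(2·0.25/65) = 0.088, or 8.8 points. In general, a 2-SD imbalance shifts the unadjusted difference by 2·√R²·√(0.2752/65) = 0.130·√R², where 0.2752 = 0.72·0.28 + 0.92·0.08. That is about 3, 4 and 6 points at R² = 0.05, 0.10 and 0.20, against a planned difference of 20 points.

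**7. Sparseness.** Expected failures are 65·0.28 = 18.2 (TVM) and 65·0.08 = 5.2 (mTVM), about 23 in all. At OR 2, 3 and 4, at least one grade had no mTVM failure in 59%, 74% and 83% of simulated trials. A continuity-corrected CMH test had only 80–85% power across OR 1–4, below plain chi-square at each OR.

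**The case against.** The strongest defence is that nothing here is wrong. A chi-square or Fisher test is valid under randomization, suits a binary endpoint and matches the approach used for the sample size. Chance imbalance is already part of the sampling variation that the test allows for, and its simulated type I error is near 5%. A 2-SD imbalance is roughly a 5% event. All of this stands.

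A reader might go further than the document allows in four ways:

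- **That the unadjusted result would be biased or invalid.** It would not be.
- **That the trial has little power to spare.** At the planned rates, chi-square has about 86% power at 65 per arm and 93% at 81, against a target of 80%.
- **That severity is known to predict cure.** The protocol gives no figure or statement on this. With OR 1.5 or less the gain is nil.
- **That every woman is graded and allocation is unrestricted.** The words about all cases attach to the demonstration of SUI, and Table 1 lists no severity grade, so grading of everyone is a natural reading and not a literal statement. The randomization sections do not say whether the list is simple or blocked.

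It is also fair to object that stratifying a primary test with about 5 failures in one arm adds sparse cells and analyst choices. That holds against a loosely worded proposal: without a merging rule and a statement on continuity correction, the change could cost more power than it gains. It does not hold against one stratifier with both points fixed in advance. Nor does a Mantel-Haenszel risk difference bring in the conditional odds ratio that a logistic model would.

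Adjusted analyses are often left to an analysis plan that is not shown. Here, however, the article itself names the test, so the point concerns a stated choice.

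**Conclusion.** The point holds as a modest improvement to a stated method. The primary SUI cure test is fixed as unadjusted, a baseline form of the endpoint is described as graded before surgery, and no stratification is stated. Using the grade would change power at 65 per arm from about 86% to 86–90%: nothing at an OR of 1.5 or below, about 1–4 points at 2–4, and a negligible loss if severity is not prognostic. These figures rest on the assumed three grades at 30/40/30%, the assumed odds ratios and the protocol's 72% and 92%. The planned analysis remains valid if nothing is changed.

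**What to change.** Before outcome data are seen, state in the Statistical analyses section that:

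1. the primary test of SUI cure is a two-sided Cochran-Mantel-Haenszel test **without continuity correction**, stratified by baseline SUI severity grade;
2. the effect is reported as the Mantel-Haenszel risk difference with its 95% CI;
3. a sparse grade is merged with its neighbour by a prespecified rule, applied to counts that are blinded to arm;
4. the unadjusted chi-square or Fisher test is kept as a sensitivity analysis.

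Confirm as well that the grade is recorded before surgery for every randomized woman, since Table 1 does not list it.

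The cost is a few sentences and a little more analysis work, with no extra patients; if the grade is recorded as described, no new data are needed. The downsides are sparse strata in the mTVM arm and no gain if severity does not predict cure.

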### Secondary and tertiary endpoints

The secondary measurement outcome will comprise the intraoperative findings and postoperative factors. As concerns the long-term postoperative complications of the mesh procedures, we will determine the extrusion rate, the presence of de novo urge symptoms (DNUS) or urinary tract infection (UTI), and the need for reoperation. The diagnosis of DNUS will be set if detrusor pressure changes are detected in cystometrographic pressures after the surgeries. The postoperative complications that will lead to reoperation will be infection, recurrent descent or incontinence, implant extrusion, chronic pelvic pain, and total retention. Operative and perioperative complications (six weeks after the procedures) described after TVM vs mTVM will be collected; overall frequency within all the cases will be calculated and severity will be graded using the IUGA classification comprising all the follow-up periods [27].

The subjective cure for prolapse and incontinence will be measured with a significant enhancement of the Pelvic Organ Prolapse/Urinary Incontinence Sexual Questionnaire (PISQ-12) and Pelvic Floor Distress Inventory (PFDI) scores. The PISQ-12 and PFDI are validated to assess the impact of SUI symptoms on quality of life and sexuality and relate well to the prolapse symptoms. Previous research has demonstrated that the questionnaires correspond well with grade of prolapse and urodynamic findings [5, 13, 17]. Our research group has assessed the validity of the questionnaires in screening for subjective genitourinary symptoms (unpublished data). To guarantee blinding of the tertiary outcome, the participant will complete the questionnaire without the outcome assessor present and seal it in an envelope, which will be given to research staff. The subjective outcome assessment is largely performed by participant-completed questionnaire, thus avoiding interviewer bias.

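### The secondary events are given both a Chi-square/Fisher test and a six-point repeated-measures ANOVA that does not suit them, and the log10 step for the questionnaire scores has no rule for zero

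*Protocol article*

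**What the plan says.** The Statistical analyses section of the protocol article gives two instructions for secondary outcomes.

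- In its second paragraph: "Primary and secondary outcome analysis: the Chi-square test or Fisher’s exact test will be employed to identify any objective outcome differences among groups".
- In its third paragraph: "Univariate-repeated measure analysis of variance (ANOVA) will be used to determine the secondary outcome between and within the two groups", to be done "at six endpoints (before intervention and during follow-up clinical appointments 1–5 following intervention".

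The section Secondary and tertiary endpoints describes the secondary outcome as findings during surgery and factors after it. On long-term complications it says "we will determine the extrusion rate, the presence of de novo urge symptoms (DNUS) or urinary tract infection (UTI), and the need for reoperation". De novo urge is to be diagnosed from cystometric pressure changes after surgery.

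For the questionnaires, if normality is violated, "PISQ-12 and PFDI scores as tertiary outcomes will be normalized by log transformation (log10(x"). No constant is added and no rule for a zero score is given. Missing values are to be filled by LOCF. The Statistical analyses section calls these scores tertiary. The Abstract lists questionnaire-based cure among the secondary endpoints.

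**The concern.** A repeated-measures ANOVA with a pre-operative point compares changes in the mean of a measured quantity between arms. Extrusion, reoperation and de novo urge cannot exist before the operation, so their first reading is zero for every woman. Urine culture is taken at recruitment, but current urinary infection is an exclusion criterion, so that first reading is constant too. The later readings are zeros and ones, mostly zeros.

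With two methods assigned to one class of outcome and no statement of which governs, the article permits two p-values for the same complication, and the two tests do not behave alike. Complications are the safety side of the comparison, so this choice should be fixed before the data are seen.

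The log step raises a separate question. A symptom score of zero would be the best result a woman can report, and it is the one value the stated formula cannot handle.

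**Working it through.** **1. Can Table 1 supply six readings?**

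| Item | Scheduled at | Readings |
|---|---|---|
| Adverse events | surgery, 6 weeks, 6 months, 1, 2, 3 years | 6, none before surgery |
| Urodynamics (basis for de novo urge) | recruitment, 1 year, 3 years | 3 |
| Urine culture | recruitment, 6 months, 1, 2, 3 years | 5 |
| PISQ-12 and PFDI | recruitment, 6 weeks, 6 months, 1, 2, 3 years | 6 |

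Only the questionnaires match the ANOVA's stated pattern of one pre-operative and five follow-up points. De novo urge has two post-operative readings. If its unscheduled visits were treated as missing, LOCF would carry the pre-operative absence of urge into the 6-week and 6-month visits.

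**2. How does the ANOVA behave on such events?** The article gives no figure to reproduce, so this is a simulation under stated assumptions:

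- 65 women per arm, as in the Abstract (the sample size section ends at 81);
- six points, the first fixed at zero;
- an event that stays present once it occurs;
- the same 3-year cumulative rate in both arms, reached in five equal steps;
- 4,000 runs per rate.

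The group-by-time statistic is F = (SS group×time / 5) / (SS error / 640), where 5 = 6 − 1 and 640 = (130 − 2) × 5. Rejection rates at a nominal 5%:

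| Cumulative rate (assumed) | Group-by-time, uncorrected | Group-by-time, Greenhouse-Geisser | Between groups |
|---|---|---|---|
| 5% | 8.6% | 3.0% | 3.6% |
| 10% | 8.3% | 4.0% | 4.3% |
| 20% | 8.4% | 4.5% | 4.7% |

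The mean Greenhouse-Geisser epsilon was 0.39 to 0.47, where 1 would mean that the sphericity assumption holds. The uncorrected test therefore rejects too often. The corrected test and the between-group test stay below 5%.

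**3. What does log10(x) do at zero?** log10(0) has no finite value. The article gives no score range for either questionnaire, so an attainable zero on PFDI is an assumption. So is the share q of women who score zero at a visit, taken here as 5% to 20%. If a woman with any undefined value leaves a complete-case ANOVA, the loss out of 130 would be:

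- the same women score zero each time: 130 × q = 6.5 to 26;
- zeros independent over five visits: 130 × (1 − (1 − q)^5) = 29.4 to 87.4.

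If zeros occur only among cured women, with the objective cure rates of 92% and 72% from the sample size section standing in for symptom relief, the number per arm of 65 is:

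- modified operation: 65 × 0.92 × q = 3.0 to 12.0;
- comparator: 65 × 0.72 × q = 2.3 to 9.4.

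These counts show who would be affected. They do not measure bias.

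**The case against.** The strongest reply is that a valid test for complications is already in the plan. Chi-square or Fisher's exact test is prescribed for secondary objective outcomes, and it suits yes/no events. That stands. A reader might infer that the complications cannot be validly analysed at all, or that the ANOVA would yield nothing interpretable. Neither is supported: Fisher's test is there, and the ANOVA can be computed, with acceptable error rates once corrected. A sphericity correction may also be specified in an analysis plan that is not shown.

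It can also be said that the ANOVA sentence was meant for the scores. It stands in the paragraph on continuous data, directly after the sentence on PISQ-12 and PFDI; its six points match the questionnaire schedule; and the Abstract calls questionnaire outcomes secondary. This is plausible. But the endpoint section and the analysis section label the questionnaires tertiary, so read literally the sentence applies to the complications. The text has to settle this.

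On the transformation, the step is conditional on non-normality, zero is not shown to be attainable, and the article does not say that LOCF applies to undefined transformed values. All of that stands. A reader might infer that the questionnaire comparison is biased towards no difference by some stated amount. That would need zero rates and score distributions that the documents do not give.

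Two further readings do not hold. One is that "The repeated measure design with seven points in time allows us to monitor how patients change over time" is a slip for six. Table 1 has seven columns (recruitment, surgery and five follow-ups), both gynaecological examination rows are marked in all seven, and the sentence itself refers to the period before and during the intervention. Six for the ANOVA and seven for the design are compatible. The other is that "The subjective cure for prolapse and incontinence will be measured with a significant enhancement" must mean a group-level test result. The primary endpoint section uses the word significant for a measured threshold of more than 3 cm, so a per-patient cut-off may be intended and left to the full protocol.

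**Conclusion.** The point holds as a defect in two written rules.

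First, the article assigns two methods to the secondary outcome. One of them, the six-point ANOVA with a pre-operative reading, does not suit the events listed there. Uncorrected, its group-by-time test had a simulated type I error of about 8.3% to 8.6%. That figure depends on the assumed cumulative rates of 5% to 20%, on events that persist once they occur, and on 65 women per arm.

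Second, the log10 transformation is undefined at zero. If normality fails and zero is attainable on PFDI, women with the best result could be dropped or, if treated as missing, given an earlier score. The direction and size of any resulting bias are not known from the documents.

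The inconsistent secondary/tertiary label for the questionnaires adds to the first problem, because it decides which outcomes the ANOVA sentence covers. The primary incontinence cure test is untouched. The change should be made but is modest.

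**What to change.** - **Complications:** report number and percent per arm over follow-up, with the risk difference, its 95% confidence interval, and the Chi-square or Fisher's exact test already planned. State that the repeated-measures ANOVA does not apply to them.
- **PISQ-12 and PFDI:** restrict the repeated-measures analysis to these scores. Use a mixed model at the five post-operative visits with the baseline score as covariate, on the raw scale. If a transformation is kept, choose one that is defined at zero and write down the rule.
- **Labels:** call the questionnaires either secondary or tertiary, consistently in the Abstract, the endpoint section and the Statistical analyses section.

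The cost is changes of text and slightly more analysis work. No new data or visits are needed. The changes should be made before the outcome data are analysed.
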